#### Power calculation

We chose to perform a full census of the district’s 1,733 remote communities based on a set of simulation-based power calculations. Briefly, this involved simulating the population of eligible women (including their complete birth histories), taking a complex sample from this population, and running the planned statistical analysis on this sample. This entire procedure was performed repeatedly, and power was estimated as the percentage of simulation replicates for which the null hypothesis was rejected. Power was estimated as 82% for a full census. The treatment effect was assumed to be a 25% decrease in the hazard of U5M, linearly decreasing from the start of the program to six months and constant thereafter. The baseline mortality rate was set at roughly 100 deaths per 1,000 live births. The simulated dataset included random intercepts at the level of the community and at the level of the community-treatment interaction, allowing for heterogeneity in terms of both the baseline mortality rate and the effectiveness of the intervention.

### Inclusivity in global research

Additional information regarding the ethical, cultural, and scientific considerations specific to inclusivity in global research is included in S1 Checklist.

## Discussion

This study will estimate the impact of Liberian NCHA program including iCCM and perinatal care support in remote Liberia on U5M. The staggered implementation of scale up within Grand Bassa offers a unique opportunity to evaluate the effectiveness of this program on a population scale. The analysis will allow us to evaluate the implementation of a critical healthcare delivery program by the Liberian Ministry of Health on U5M within the target communities.

There are multiple unique aspects of this study which will enhance both its scope and generalizability. The total population census with a program coverage of 1,753 communities and 23,702 households in the Grand Bassa county of Liberia, we will take advantage of a notably large sample size. The fact that the NCHA program is being implemented staggered across eight study health districts in four phases also gives us the opportunity to use a mixed effects Cox proportional hazards model with a random effect by community and district fixed effects to compare the intervention effect both within and between geographic regions. Finally, the use of U5M as the primary outcome, as opposed to intermediate health care delivery indicators and process measures, will allow us to measure the population level impacts of such a CHW-based child health care program at scale.

There are limitations to the design of this study. First, the order of implementation by district was non-randomized. Because the districts with the worst health outcomes were targeted by the intervention first, our estimate of the intervention effect estimate may be biased. Nonetheless, the stepped approach to implementation, availability of pre- and post-implementation data in the districts, and our use of district fixed effects and community covariates all enhance the causal inference of this study design. Second, the random effects at the community level rely on an assumption of minimal correlation of unobserved confounders with NCHA program exposure. Third, the data for our outcome relies on endline survey data, thus selective migration by intervention implementation date potentially causes bias in the main estimates. To address this, we will include a sensitivity analysis that limits the analysis only to those mothers who report living in the implementation area for the full study period. Third, U5M is assessed in the survey design by recall of such events in the last four years. There may be bias associated with mothers not remembering the correct birth/death dates of children. We will assume that this recall bias (and related biases, e.g. mothers’ reluctance to discuss child deaths) is minimal and does not differ significantly by geography or intervention status date. To mitigate to this source of bias and increase the validity of death reporting, we will employ a landmark event calendar, which has been previously shown to improve precision of event reporting [17]. Finally, the fidelity of implementation is not a component of this impact study, but is the focus of ongoing program evaluation to measure dose, coverage and effect of contextual factors including health facility readiness and the COVID-19 pandemic.

Prior studies have demonstrated improvement in process measures from implementation of small scale governmental CHW programs in similar settings including Liberia [18, 19]. Whereas Nyqvist, Guariso [11] were able to randomize program exposure across communities, the program was different from our evaluation in that it is was operated by a non-governmental organization. Our study will add to the literature by providing evidence from a large scale, governmental-led CHW program.

In summary, this study will provide invaluable insight on the impact of large-scale, publicly operated CHW programs on child health. Results will be directly applicable both to the Liberian Ministry of Health, as well as to other governmental entities supporting similar CHW-based rural child health programs in the region. Because such rural areas are known to face the largest U5M burden in many sub-Saharan countries, our study results will directly respond to the need to understand the optimal methods of improving health care among many of the most vulnerable populations in the region.

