## Method

### Study setting and population

Data collection did start in Grand Bassa county in January 2022. The county encompasses an area of 7,936 square kilometers and had an estimated total population of 224,839 in 2008 [15]. The target population of the NCHA are households in remote communities. Remote communities are defined as having a distance of at least 5 km to the nearest health facility. Based on a county-wide community GIS mapping exercise conducted by LMH immediately before program implementation, 1,733 communities were identified as remote, totaling 23,702 households and approximately 13,400 people and 20,900 children under the age of five years. The remote population is predominantly poor and levels of education are low. In S1 Table we show descriptive statistics for the study population. The study has been registered at clinicaltrials.gov [NCT: NCT05123378]. Approval for the study was obtained from the University of Liberia-Pacific Institute for Research and Evaluation Institutional Review Board (18^th^ of November 2021, 18-11-140) and Advarra Institutional Review Board (25^th^ of January 2021, Pro00048901), United States.

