### Community health worker intervention

#### The program

As part of the post-Ebola investment plan for building a resilient health system in Liberia 2015–2021, the MOH prioritized the establishment of a robust cadre of community health workers in remote communities that were situated more than 5 km from the nearest health facility. Through the NCHA program, members of remote communities select their CHA. Those selected by their communities have to fulfil eligibility requirements, including being permanent residents in the community, aged 18 to 50 years, possess basic writing and math skills, be physically and mentally fit and must be fluent in the dialect spoken in their community. Once selected, CHAs complete a standardized training curriculum in community health and surveillance, child health and maternal and neonatal health. Services are covering treatment of diarrhea, ARI, and malaria following iCCM protocols, as well as family planning and birth preparedness. Since 2020 COVID-education and -referral has also been included in the CHAs work. Everyone in the communities more than 5 km from the nearest health facility is eligible to use the program directly or indirectly. CHAs are compensated with a monthly cash incentive of US $70 for about 20 hours of work per week. Program implementation is preceded by community engagement activities, which involves obtaining the support and advice of community leaders.

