### Study design

Starting in January 2022, we will conduct a census to assess U5M among the children of all women who complete the survey. The study is registered at clinicaltrials.gov (NCT05123378).

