### Data collection

#### Impact assessment survey

In the 2022 impact assessment survey, we will collect data on births and child deaths from mothers aged 15 to 49 in all eight health districts of Grand Bassa (see S2 Table). We will use a survey tool based on the validated Demographic and Health Survey (DHS) that includes a full birth history, as well as questions on socioeconomic status, education, and covariates that we expect to be associated with our endpoints. We will supplement this dataset with geographic and community-level covariates obtained through a separate district mapping process. Whenever possible, the survey will be conducted in Liberian English. If a respondent speaks only Bassa, a local dialect without a commonly used written form, the enumerator will do on-the-spot translation, which they will be trained to do. We will obtain death dates using the standard Demographic and Health Survey approach, augmented with recall-enhanced elicitation. For the recall-enhanced elicitation, mothers are asked to recall all their children death dates if occurred within the last four years. The same method has been applied in similar settings by Nyqvist, Guariso [11]. Anchoring methods with landmark events will be used in the questionnaire to foster the outcome documentation [17]. We will use a calendar developed specific to Grand Bassa County, providing landmark events helping to clearly mark the reference period. Reluctance to report U5M is not expected to vary systematically by program implementation date. All participants gave (verbal/written) informed consent to participate. Written informed consent was obtained from a parent or guardian for participants under 16 years old.

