### Statistical analysis

The Liberian NCHA intervention and data collection will provide a survival data set for U5M at the community level, covering a time period from January 2018 till August 2022. To estimate program effects on U5M we will use a mixed effects Cox proportional hazards model.

Our primary outcome of interest will be U5M at the community level. Our primary exposure of interest will presence of the NCHA program. Sensitivity analyses will allow for the possibility of a time-varying treatment effect. Children will be included in the risk set from their date of birth or January 2018 (starting date of the panel), whichever is later, until their death, fifth birthday or date of the survey in 2022. Children born before implementation who remain under observation at the implementation date in their community will provide observation time to both the pre- and post-observation time periods. We will fit a mixed effects Cox proportional hazards model with a random effect at the community level to estimate effect of the NCHA program on mortality. To mitigate bias due to unobserved time-invariant confounders that were caused by the non-randomized implementation schedule of the program, we will include a fixed effect at the district level. We will also control for baseline demographic and geographic covariates.

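### The check offered against selective migration covers women who arrived, not women who left or died before the 2022 survey

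*Protocol article*

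**What the plan says.** Under Study design, the article says "we will conduct a census to assess U5M among the children of all women who complete the survey". The Impact assessment survey section names the informants: "we will collect data on births and child deaths from mothers aged 15 to 49 in all eight health districts". No other informant is described, and nothing is said about tracing women who left, proxy reports, or children whose mother has died.

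Under Statistical analysis, the data set is described as "covering a time period from January 2018 till August 2022". The Implementation section puts the roll-out between September 2018 and June 2022.

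The Discussion states the limitation openly: "the data for our outcome relies on endline survey data, thus selective migration by intervention implementation date potentially causes bias in the main estimates". It offers one remedy: "To address this, we will include a sensitivity analysis that limits the analysis only to those mothers who report living in the implementation area", with residence required over the whole study period.

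**The concern.** The source of the bias is that outcomes are seen only for women present at endline. Two groups are affected: women who came in during the window, and women who went out of it by moving away or dying. The restriction sorts the interviewed women by residence history, so it deals with the first group. The second group is absent from both the main and the restricted analysis, and comparing the two says nothing about it. The restricted sample consists wholly of women who stayed and survived, so the same selection applies to it.

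Loss through exit is also not even across the comparison. In any one community, pre-program time comes before post-program time, so it has had longer to lose its informants.

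If leavers had higher child mortality than stayers, pre-program deaths would be under-counted more and the hazard ratio would move towards 1. If leavers had lower child mortality, the benefit would be exaggerated. A restricted result that agrees with the main one could then be read as evidence against migration bias, when only one side of migration has been examined.

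**Working it through.** **The plan's own figures.** The article gives no exit rate, maternal death rate or comparison of leavers with stayers, so there is no figure to reproduce on this point. The 82% power is used only as a yardstick in step 5. It cannot be reproduced, because the simulation's variance components and significance level are not given.

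**1. Inputs.**
- From the article: window opening January 2018; survey from January 2022 (48 months later), data to August 2022 (about 55 months); design hazard ratio 0.75.
- Assumed: interview at T = 51.5 months, the midpoint of 48 and 55; program start at s = 25.75 months, mid-window; exit (moves out plus deaths) d = 2% or 5% of mothers per year; leaver-to-stayer child-mortality ratio r = 0.7, 1, 1.5 or 2.

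**2. Lag and loss.** Mean lag to interview:
- pre-program = (T − s/2)/12 = (51.5 − 12.875)/12 = 3.22 years
- post-program = (T − s)/(2 × 12) = 25.75/24 = 1.07 years

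The difference is T/2 = 25.75 months whatever the start date. Share of child-time lost is L = 1 − exp(−d × lag):
- d = 2%: 6.2% pre, 2.1% post
- d = 5%: 14.9% pre, 5.2% post

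**3. Effect on the hazard ratio.** The true hazard is the stayers' hazard × [(1 − L) + L × r]. Hence

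observed HR = 0.75 × [1 + Lpre(r − 1)] / [1 + Lpost(r − 1)].

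| r | d = 2% | d = 5% |
|---|---|---|
| 0.7 | 0.741 | 0.728 |
| 1 | 0.750 | 0.750 |
| 1.5 | 0.765 | 0.785 |
| 2 | 0.780 | 0.819 |

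For r = 2 and d = 5%: 0.75 × 1.1487/1.0522 = 0.819. With starts at 8 or 38 months the same cell is 0.814 or 0.822, so the start date matters little.

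**4. A second model.** Take four evenly spaced phases from September 2018 to June 2022 (spacing assumed; the schedule figure is not shown) and an interview around May 2022. Pooled loss is 5.2% pre against 2.8% post at 2% per year, and 12.5% against 6.8% at 5%: a smaller gap in the same direction. Now let bereaved mothers leave at twice the rate of others. With district effects and no calendar-time term, a true 0.75 appears as 0.78 (4% against 2% per year) or 0.84 (10% against 5%). Adding calendar month returns 0.75 in both cases.

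A calendar term does not remove exit that depends on the program. If the excess exit of bereaved mothers is 5% per year before the program and 2% after, the calendar-adjusted hazard ratio is 0.738. With the two rates reversed it is 0.763.

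**5. Size against precision.** If 82% power refers to a two-sided 5% test (assumed), the standard error of the log hazard ratio is 0.2877/(1.96 + 0.915) = 0.100. The shifts in step 3 then run from ln(0.728/0.75)/0.100 = −0.3 to ln(0.819/0.75)/0.100 = +0.9 standard errors.

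**The case against.** The strongest reply is that the Discussion names migration that differs by implementation date, whereas a constant exit rate produces only a calendar trend in ascertainment. A calendar-time term removes that, and a condensed article need not list every model term. This stands: the figures in step 3 apply to an analysis without such a term, and its absence from the article does not prove that it is absent from the full plan. Program-related exit would survive the term, but in the cases tried in step 4 it moves the hazard ratio by only about 0.01.

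Several other points also stand:
- A reader might infer that the larger pre-program loss is itself a bias. It is not; with r = 1 the hazard ratio stays at 0.75.
- Most of the assumed shifts are under half a standard error, and the larger ones run towards no effect.
- The survey covers all remote communities in the county, so a woman who moves between them may still be interviewed. Only exit from the remote population counts.
- A reader might infer that the program changed which mothers survived, since the training includes maternal and neonatal health. Nothing in the article shows that maternal deaths are numerous enough to matter.
- The authors disclose the limitation and call the restriction a sensitivity analysis.

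None of this makes the restriction informative about women who left or died, and the article says that it will address the problem.

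**Conclusion.** The point holds in a limited form. The stated check covers in-migration only; out-migration and maternal death are outside its reach, and nothing else in the article deals with them. That conclusion follows from the text and needs no assumption.

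The size does rest on assumptions. With exit of 2-5% per year, leaver-to-stayer mortality ratios of 0.7 to 2.0 and no calendar-time term, a true 0.75 would appear as about 0.73 to 0.82. If bereaved mothers leave at 10% against 5% per year, it reaches 0.84. The direction is unknown.

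It would be too strong to say that the primary estimate is biased, or that a benefit would be manufactured. The article holds no data on exit that would support either. What is wrong is the claimed scope of the remedy.

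**What to change.** 1. In the Discussion, state that the restriction to full-period residents covers in-migration only, and that women who left or died before the survey are not addressed by it.
2. Pre-specify a bounding (tipping-point) table for the primary hazard ratio over assumed exit rates and leaver-to-stayer child-mortality ratios. Include exit that differs by program status, since a calendar-time term does not remove that part. Report the values at which the conclusion changes.
3. Where available, use the pre-program mapping ("1,733 communities were identified as remote, totaling 23,702 households") against the 2022 household count to inform the range of exit rates. This is a rough net figure only. It mixes in new households and misses a mother who leaves or dies while her household remains. It also does not cover the time before mapping, and the article does not say that household arrival dates are recorded.

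Cost: a wording change and a short extra analysis, with no field work. The downside is that the result may look less certain.

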#### Implementation

The Liberian NCHA program was initiated in a stepwise manner across the eight districts of Grand Bassa County by the government of Liberia beginning in September 2018. It is planned to conclude in June 2022 (Fig 1). We will take advantage of this staggered implementation to form a study design similar in structure to a stepped wedge cluster randomized trial. However, the order of implementation was not randomized; judged by the Liberian MOH districts with more need for health interventions were prioritized in the intervention roll out. The staggering of implementation was conducted for operational and logistical reasons, rather than to facilitate an evaluation.

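### Recall error is assumed not to differ by intervention status, but pre-program time lies 2.0 to 2.3 years further from the single 2022 interview, and no stated model term or sensitivity analysis covers this

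*Protocol article*

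**What the plan says.** The outcome is collected retrospectively in one round (Study design): "Starting in January 2022, we will conduct a census". The resulting survival data set is described under Statistical analysis as "covering a time period from January 2018 till August 2022", and children are followed "until their death, fifth birthday or date of the survey in 2022". Under Implementation, the roll-out is dated "by the government of Liberia beginning in September 2018" and "It is planned to conclude in June 2022". The Discussion describes it as "staggered across eight study health districts in four phases".

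On recall, the limitations paragraph of the Discussion accepts that birth and death dates may be misremembered and that mothers may be reluctant to speak of deaths. It then assumes that this bias "is minimal and does not differ significantly by geography or intervention status date", and offers a landmark event calendar as mitigation. The Impact assessment survey section has a related sentence: "Reluctance to report U5M is not expected to vary systematically by program implementation date".

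The model under Statistical analysis has a community random effect, a district fixed effect, and baseline demographic and geographic covariates. It names no calendar-time term and does not state the time scale of the Cox model. The named sensitivity analyses concern a time-varying program effect and migration.

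**The concern.** The program effect is estimated by setting pre-implementation child-time against post-implementation child-time, and both are reported at the same interview. Within a community the pre-program part always comes first, so recall distance is tied to intervention status by the design itself. If reporting of deaths fades with time, recall error differs by intervention status even if every district recalls equally well.

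The landmark calendar helps a mother place an event she reports. It does not by itself recover a death she leaves out. The enhanced death-date questions reach back four years. For interviews after January 2022 they therefore miss up to about eight panel months (January to August 2018), all before the first program start, which adds to the asymmetry.

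Under-reporting of older deaths lowers apparent pre-program mortality and raises the estimated hazard ratio. A weak or null finding about a national program could then be partly a reporting artefact, and nothing in the stated plan would show it.

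**Working it through.** **The plan's own figure.** The stated 82% power cannot be reproduced, because the variance components and significance level are not given. An unclustered calculation with 20,900 / 5 × 0.10 × 4.0 to 4.67 years = about 1,670 to 1,950 deaths gives over 99.9%. About 400 to 476 events would suffice for 82%, so the plan's figure implies a variance inflation of roughly 4 to 5. This shows no error, and the point does not depend on it. Taken as given, with two-sided alpha 0.05 assumed, 82% at a hazard ratio of 0.75 implies SE(log HR) = 0.288 / (1.96 + 0.915) = 0.100.

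**Step 1: the recall gap.** Let T be the months from January 2018 to interview and s the month of program start.

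- Midpoint of pre-program time before interview: T − s/2.
- Midpoint of post-program time before interview: (T − s)/2.
- Difference: T/2, whatever s is.

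The phase dates are in a figure that is not shown, so four evenly spaced starts from September 2018 (month 8) to June 2022 (month 53) are assumed. For T = 56 (end of August 2022):

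| Start month | Pre (years) | Post (years) | Gap (years) |
|---|---|---|---|
| 8 | 4.33 | 2.00 | 2.33 |
| 23 | 3.71 | 1.38 | 2.33 |
| 38 | 3.08 | 0.75 | 2.33 |
| 53 | 2.46 | 0.13 | 2.33 |

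For an interview in January 2022, T = 48 and the gap is 2.0 years. A community interviewed before its start has no post-program time and adds nothing to this within-community contrast.

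**Step 2: effect on the hazard ratio.** The omission rate per year of recall, f, is an assumption (1% to 5%). With district effects and no time term, the distortion is close to one gap's worth of omission: estimated HR ≈ true HR × (1 − f)^(−T/2), with T/2 in years. For f = 2% and T/2 = 2.33: 0.75 × 0.98^(−2.33) = 0.786.

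This was checked by a Poisson model on expected deaths by district phase and month (20,900 children, 0.021 deaths per child-year from roughly 100 per 1,000 over five years, constant effect, one interview date), with T = 56. Power is Φ(|ln HR| / 0.100 − 1.96).

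| Omitted per year | True HR 0.75: estimate | True HR 1.00: estimate | Power when true HR is 0.75 |
|---|---|---|---|
| 0% | 0.750 | 1.000 | 82% |
| 1% | 0.768 | 1.024 | 75% |
| 2% | 0.786 | 1.048 | 67% |
| 3% | 0.805 | 1.074 | 58% |
| 5% | 0.845 | 1.127 | 39% |

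At 5%, T = 54 gives 0.842, and the formula with T = 48 gives 0.75 × 0.95^(−2) = 0.831.

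**Step 3: the same data with recall distance modelled.** Adding half-year bands of time before interview returns 0.750 to 0.752 at every omission rate when the truth is 0.75. Calendar-month effects, or a baseline hazard on the calendar scale, likewise keep the estimate at the truth when fading is common to all districts.

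**Step 4: the price.** With bands, SE(log HR) rises from 0.060 to 0.083 (T = 56) or from 0.063 to 0.084 (T = 54), an increase of 38% or 33%. These SEs come from an unclustered model, so only the ratio should be carried over. Applied to 0.100, an increase of 30% to 40% gives 0.13 to 0.14, and power at 0.75 of about 60% to 54%.

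**The case against.** Several points on the other side are sound and limit what can be claimed.

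- **Condition on the model.** The bias arises only if calendar time is left out. The article does not state the Cox time scale, and a fuller analysis plan may do so. A reader might infer that the primary estimate is certainly biased; the documents do not support that. What stands is that none of the listed terms removes the bias.
- **Meaning of the assumption.** The wording refers to an intervention status date, and the survey section speaks of implementation date. The authors may have meant early against late districts. On that reading they do not assert equality before and after; they leave the difference unaddressed. Either way the sentence needs repair.
- **Direction.** It is tempting to call this bias towards no effect. That is right for a truly protective program. With a true hazard ratio of 1, the same omission gives a value above 1, away from the null. The general statement is upward bias.
- **Omission is assumed.** The article speaks of misremembered dates and of reluctance. Misdating can move deaths either way across the start date. The birth history asks about each birth, which should limit omission. At 1% per year the shift is small (0.75 to 0.77), and the authors claim only a minimal bias with no significant difference, not exact equality.
- **Size of the gap.** A reader might take 2.3 years to hold in every district. It is the upper end, and some late-phase communities interviewed early have no post-program time.
- **Overlap.** With one survey in 2022, bands of time before interview are nearly calendar periods, so the first remedy is close to period adjustment.

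None of this removes the structural link between recall distance and intervention status.

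**Conclusion.** The point holds in conditional form. The design places pre-program time 2.0 to 2.3 years further from the interview than post-program time in every community that has both. The assumption of no difference by intervention status therefore conflicts with the design on one reading and leaves the gap uncovered on the other. No stated model term or sensitivity analysis deals with it.

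If older deaths are omitted more often and calendar time is not modelled, the hazard ratio is biased upwards: from 0.75 to about 0.77 to 0.84 for 1% to 5% omission per year, and from 1.00 to about 1.02 to 1.13. Those omission rates, the phase dates, the constant effect and the common interview date are assumptions. The T/2 gap depends on none of them except the interview date.

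The power losses illustrate the same assumptions and do not show that the stated 82% is wrong.

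**What to change.** In the limitations paragraph of the Discussion, replace the claim of no difference by intervention status. State instead that pre-program time is recalled over about 2.0 to 2.3 more years than post-program time, and that greater omission of older deaths would bias the hazard ratio upwards.

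Pre-specify two sensitivity analyses:

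1. The Cox model with half-year bands of time before interview as a time-varying stratum, so that exposed and unexposed child-time at the same recall distance is compared across phases. If the full analysis plan already adjusts for calendar period, citing that would largely serve.
2. A bias analysis that re-weights reported deaths for omission of 0% to 5% per year of recall and reports the resulting range of hazard ratios.

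The cost is a change of wording and two further analyses of data already being collected. The drawback is the loss of precision in the banded fit (SE about 30% to 40% larger). It should therefore stand beside the primary fit and not replace it on this ground alone.
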